# **Secondary Endpoint**

1. Efficacy - % patient able to be weaned off pre-LDRT ventilatory or oxygen support at 3d post LDRT
2. Efficacy - % patients able to come off (or avoid) mechanical ventilation within 7 days following LDRT
3. Efficacy - % patients discharged or expired at 14d/28d post LDR

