# **PROTOCOL SUMMARY**

# **SYNOPSIS**

| Study description: | Hypothesis: Low-dose radiation therapy (LDRT) improves clinical, radiographic, and immune outcomes in hospitalized patients with covid-19 pneumonia and severe acute respiratory syndrome.  This study investigates LDRT as a selectively localized anti-inflammatory treatment to induce focal suppression of pulmonary immuno-toxicity within viral pneumonia infiltrates in hospitalized patients with COVID19.  Study: Administration of low dose whole lung radiotherapy (LDRT) for the treatment of severe COVID 19 pneumonia in patients on or requiring mechanical ventilation |
| --- | --- |
| Objectives: | To investigate safety and feasibility (primary endpoint) of low dose whole-lung radiation therapy (LDRT) in critically-ill patients with COVID-19 pneumonia, and to explore secondary efficacy endpoints: (1) clinical, (2) respiratory, and (3) outcome  **Primary Objective:**   1. To assess the feasibility and safety of administering LDRT to patients with severe Covid 19 pneumonia 2. To assess the toxicity of a single dose of LDRT administered to patients with severe Covid 19 pneumonia   **Secondary Objective:**   1. To assess improvement in oxygen requirement within 3 days following LDRT 2. To determine ability to come off mechanical (or avoid mechanical) ventilation within 7 days following LDRT 3. To determine time to discharge following LDRT 4. To determine time to death following LDRT |
| Endpoints | Primary   1. Safety/Feasibility – ability to complete LDRT without treatment related SAE 2. Toxicity – vital signs to assess clinical and respiratory status at 24h following LDRT   Secondary   1. Efficacy - ability to be weaned off pre-LDRT ventilatory or oxygen support at 3d post LDRT (% of patients) 2. Efficacy – ability to come off (or avoid) ventilatory support at 7d post LDRT (% of patients) 3. Efficacy - discharge or death by 14d / 28d post LDRT (% of patients) |
| SAMPLE SIZE | Up to 20 participants will be enrolled on this study.   - Cohort 1 (pre-Vent): Up to 10 participants - Cohort 2 (on-Vent): Up to 10 participants |
| Study population | 1. Patient with rtPCR and Xray/CT proven Covid 19 pneumonia who have not responded to conventional therapy and:   Cohort 1: would need mechanical ventilation if condition worsens (pre-Vent)  Cohort 2: has been on mechanical ventilation, but for not more than 5 days (on-Vent) |
| Phase: | Pilot Phase 1b/2 study |

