# **Secondary Objectives**

1. To determine improvement in Oxygen requirement within 3 days following LDRT
2. To determine ability to come off mechanical ventilation within 7 days following LDRT
3. To determine time to discharge following LDRT
4. To determine time to death by following LDRT

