# **End of study definition**

All eligible patients following consent will receive a single dose of LDRT within 48h of meeting eligibility and being enrolled on the study. Patients will undergo routine physical examination, vital signs and oxygenation parameters on a daily basis as part of standard of care. Observation period for the study will end on day 28 or at the time of discharge (or death), whichever comes first.

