# **STATISTICAL ANALYSIS**

Descriptive statistics will be used to determine proportion of patients experiencing toxicity, improvement/worsening of oxygenation status, weaning off oxygenation or ventilation, discharge or death on/before 14d and on/before 28d. All endpoints will be summarized descriptively, using mean, median, interquartile range, minimum/maximum, and standard deviation for continuous endpoints, and frequency and percentage for categorical endpoints. The data from the 2 cohorts will be analysed independently.

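### Secondary endpoint 3 pools discharge and death into one efficacy percentage, so the same value can describe opposite results

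*Protocol*

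**What the plan says.** Protocol section 5.1.4 (Secondary Endpoint), item 3, is labelled efficacy and is the percentage of "patients discharged or expired at 14d/28d post LDR". The synopsis (section 1.1) carries the same item, also under efficacy: "discharge or death by 14d / 28d post LDRT (% of patients". Section 16 (Statistical Analysis) lists the proportions to be described and includes "discharge or death on/before 14d and on/before 28d", without an efficacy label.

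The objectives in section 5.1.2 keep the two outcomes apart: "To determine time to discharge following LDRT" is one item and "To determine time to death by following LDRT" is the next. Neither has a matching time endpoint in section 5.1.4.

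On follow-up, section 6.1.7 states: "Observation period for the study will end on day 28 or at the time of discharge (or death), whichever comes first". Section 12.4 and footnote 4 of Table 1 add safety contact through Day 14 for patients who leave earlier.

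**The concern.** A percentage offered as evidence of efficacy should move in one direction when patients do better. This one counts a patient who goes home and a patient who dies in the same way, and only a patient still in hospital lowers it. The ordinal score in section 12 puts discharge at 1 and death at 7, so the protocol itself treats the two as opposite extremes.

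The study has no comparator. Section 17.2 and the Post Trial Access section tie wider use to the study showing benefit. A reader who meets a high value for this endpoint cannot tell from it whether it points to benefit or harm. The difficulty is greatest in the on-vent cohort, where deaths are expected to be common.

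**Working it through.** **Inputs**

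- Patients per cohort: n = 10 at full enrolment. The synopsis says "Up to 20 participants will be enrolled on this study", and 2 cohorts × (5 + 5) = 20, which agrees. Section 16 analyses the cohorts independently, so the denominator is 10. The sample size is descriptive, and there is no power calculation to reproduce.
- Mortality m in ventilated severe cases: 50% to 80% (section 2, Introduction). That figure is not tied to Day 28; using it as 28-day mortality is an assumption.
- Share q of survivors discharged by Day 28: not given in the protocol. It is an assumption, shown over its full range of 0 to 1.

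**Step 1: the endpoint as written**

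Pooled percentage = (discharged + dead) / n.

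| Discharged | Dead | Still in hospital | Pooled | Discharged % | Dead % |
|---|---|---|---|---|---|
| 10 | 0 | 0 | 100% | 100% | 0% |
| 5 | 5 | 0 | 100% | 50% | 50% |
| 2 | 8 | 0 | 100% | 20% | 80% |
| 0 | 10 | 0 | 100% | 0% | 100% |
| 8 | 0 | 2 | 80% | 80% | 0% |
| 4 | 4 | 2 | 80% | 40% | 40% |
| 0 | 8 | 2 | 80% | 0% | 80% |

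The pooled column cannot tell the first four rows apart, or the last three. The two right-hand columns can.

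**Step 2: direction of movement**

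Pooled = m + (1 − m) × q. Discharged = (1 − m) × q.

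| q | Pooled, m = 50% | Pooled, m = 80% | Discharged, m = 50% | Discharged, m = 80% |
|---|---|---|---|---|
| 0 | 50% | 80% | 0% | 0% |
| 0.5 | 50 + 25 = 75% | 80 + 10 = 90% | 25% | 10% |
| 1 | 100% | 100% | 50% | 20% |

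The pooled formula can be rewritten as q + m × (1 − q). For a fixed q it therefore never falls as mortality rises, and it rises whenever q is below 1.

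The pattern does not depend on q being equal in the two scenarios. At 80% mortality the pooled figure is at least 80% whatever q is. That exceeds the 75% obtained at 50% mortality with q = 0.5.

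**Step 3: what the records allow**

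In-hospital status can be separated at both time points. The ordinal score is taken on Days 14 and 28 while the patient is in hospital, and again at discharge. The serious adverse event form records the date of death. Deaths after discharge are a different matter: section 6.1.7 ends observation at discharge and section 12.4 stops safety contact at Day 14. The protocol therefore schedules no contact that would show a death after discharge between Days 15 and 28.

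**The case against.** The strongest reply is that the wording is shorthand for two percentages. Section 5.1.2 separates the two outcomes. The list in section 16 also pairs improvement with worsening of oxygenation, which nobody would pool. The same section promises frequency and percentage for categorical endpoints, and applied to a three-level status that gives separate figures. This may well be what the authors meant. It does not settle the matter, because the synopsis and section 5.1.4 each define one percentage joined by *or*, and no section says that two will be reported. A statistical analysis plan that split them would be departing from the protocol's definition.

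A second reply is that deaths are visible elsewhere: in the ordinal score, in the serious adverse event form and in alerts to the safety committee. That stands. The defect lies in this endpoint and not in the study's ability to detect deaths in hospital.

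A reader might also infer that the plan averages time to discharge among discharged patients only. The one stated rule for continuous data is "using mean, median, interquartile range, minimum/maximum, and standard deviation for continuous endpoints". The harm from such an average is easy to show. With discharges on Days 8, 10 and 12 and seven deaths, the median among the discharged is 10 days, yet only 3/10 = 30% were ever discharged and the median over all ten is not reached. The protocol does not specify that calculation, however. The times are objectives without a time endpoint, the rule speaks of endpoints, and methods for censoring and competing events are commonly left to a statistical analysis plan. This is a caution, not an error in the document.

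**Conclusion.** The point holds for the percentage. As written in the synopsis and section 5.1.4, and echoed in section 16, secondary endpoint 3 cannot distinguish benefit from harm: 10 discharged and 0 dead gives the same 100% as 0 discharged and 10 dead. That result rests on arithmetic alone. The example of a rise from 75% to 90% also rests on two assumptions: that half of survivors are discharged by Day 28, and that the Introduction's mortality range applies at Day 28.

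The severity is moderate. This is a descriptive secondary endpoint in a pilot, with no test, threshold or decision rule attached. Expansion and halting of cohorts depend on treatment-related serious adverse events at 24 hours. The primary endpoints and sample size are unaffected. Rating it as a barrier to starting the study would go further than the documents support.

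**What to change.** In the synopsis, section 5.1.4 and section 16, replace the pooled item with three mutually exclusive percentages of treated patients, per cohort, by 14 days and by 28 days: discharged alive, died in hospital, and still hospitalised. They should sum to 100%. Take discharge from the actual discharge record and not from the ordinal score alone, because category 1 also covers patients who are ready to leave but still in hospital. This costs wording only; the in-hospital data are already collected.

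Then decide which death measure is meant. If it is death in hospital, label it so and nothing more is needed. If it is death from any cause by Day 28, add a Day 28 vital-status contact for discharged patients and amend section 6.1.7, Table 1 with footnote 4, and sections 12.2 and 12.4. With at most 20 patients, that is at most 20 short contacts.

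For the time objectives, one sentence is enough: any summary of time to discharge covers all treated patients in the cohort and counts deaths as never discharged. The specific time-to-event method can stay with the statistical analysis plan.

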# **Exploratory Endpoint**

1. Immune response and cytokine profile will be studied retrospectively as part of “special send out tests/labs”

# **STUDY DESIGN**

# **Overall design**

This is a pilot Phase 1b/2 study to determine safety and feasibility of administering LDRT to the whole lung in a Covid 19 patient population who have progressed following administration of conventional therapy and are on ventilatory support or who are decompensating despite conventional therapy and are at risk of requiring ventilatory support to sustain life.

The rational basis is the effort to influence the pulmonary immune repertoire that is responsible for the cytokine storm responsible for the ARDS that leads to the need for mechanical ventilatory support in such patients. Previous experience at Emory University has been very favourable ^17^ Of the 10 patients (median age 78) who were requiring supplemental oxygen whose health was visibly deteriorating, received a single dose of 150 cGy. Patients were in and out of the RT unit within 10-15 minutes. Within 24h, 9/10 patients showed rapid improvement and were discharged within 12 days. No acute toxicity was observed (personal communication ahead of publication). In the meantime, there are 5 active trials studying the ability of various strategies of LDRT in Covid 19 patient population.

Our study determines to assess the safety and feasibility of administering LDRT in the LMIC setting in patients who may have different comorbidities than seen in the West, where extraordinarily expensive therapeutic agents may not be available, and where ventilators are in extremely short supply.

A single dose of LDRT is seen as a relatively inexpensive treatment in patients at the extreme end of the clinical spectrum of Covid 19 pneumonia (on ventilators or destined to need ventilator support).

Eligible patients will receive a single dose of LDRT of 100cGy which has been found to be safe and efficient is comparable settings. Patients will be followed for toxicity for the duration of their hospital stay with specific study related endpoints being determined at 24h, 3d, 7d, 14d, and 28d.

This will be a single arm, single dose pilot study involving 2 separate cohorts (Cohort 1: pre-Vent / Cohort 2: on-Vent). 5 patients will be initially enrolled on each cohort. If ≤ 1 patients experience an acute LDRT associated SAE, an additional 5 patients for a total of 10 will be enrolled.

Special labs will be collected from participants for future testing as biological correlates of response of progression.

The RT section at AKUHN has experience treating Covid 19 patients in full compliance with current infection control guidelines. In addition, we also have experience treating ventilated patients under urgent/emergent clinical setting and would thus be able to treat the patient population described in this protocol.

# **Data Safety Monitoring Committee (DSMC)**

A Data Safety Monitoring Committee (DSMC) composed of 3 individuals (clinician, clinical investigator, statistician) not involved in the study will be constituted that will review the outcome of each of the first 5 patients in each cohort at 24h following treatment. If >1 of the initial 5 patients experience an SAE felt to be related to LDRT by the investigator and/or DSMC, the study will be halted. If ≤ 1 patients experience a related SAE, a total of 10 patients in each cohort will be enrolled. Any SAE observed in any of the additional patients will be reported to the DSMC for review and discussion.

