| Description of sites/facilities enrolling patients: | 1. AKUHN – a collaborative effort of the Clinical Research Unit, Dept. of Haematology-Oncology (radiation therapy section), infectious diseases, critical care |
| Description of study intervention: | 1. Single dose of 100 cGy LDRT administered to both lungs within 48h of determining eligibility 2. Cohort 1 : 5 patients will be treated. If acute treatment related SAE is observed in ≤1 of 5 patients, additional 5 patients will be treated. 3. Cohort 2 : 5 patients will be treated. If acute treatment related SAE is observed in ≤1 of 5 patients, additional 5 patients will be treated.   If > 1 of the initial 5 patients in either cohort experiences acute treatment related SAE, enrollment to that cohort will be halted. |
| Study Duration: | 3 months |
| Participant duration: | 28d from enrollment |

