# **SAMPLE SIZE**

This is a pilot Phase 1b/2, proof of principle, study to determine safety and feasibility of a single dose LDRT for the treatment of severe Covid 19 pneumonia patients who have nearly exhausted conventional available options. Sample size is based on having sufficient patients to reasonably provide descriptive data for feasibility, toxicity and indication of efficacy:

- Cohort 1 (pre-Vent): 5 patients will be treated. If acute treatment related SAE is observed in ≤ 1 of 5 patients at 24h following LDRT, then 5 additional patients will be treated.
- Cohort 2 (on-Vent): 5 patients will be treated. If acute treatment related SAE is observed in ≤ 1 of 5 patients at 24h following LDRT, then 5 additional patients will be treated.

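### The five-patient halting rule is stated with conflicting counting windows and halt scopes, and after patient five stopping rests on DSMC discretion with no preset count

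*Protocol*

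**What the plan says.** The same gate appears in five places in the protocol.

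- **Section 15 (Sample size)**, for each cohort: "If acute treatment related SAE is observed in ≤ 1 of 5 patients at 24h following LDRT, then 5 additional patients will be treated".
- **Section 1.1 (Synopsis)**: "If acute treatment related SAE is observed in ≤1 of 5 patients, additional 5 patients will be treated", followed by "If > 1 of the initial 5 patients in either cohort experiences acute treatment related SAE, enrollment to that cohort will be halted".
- **Section 6.1.1 (Overall design)**: "If ≤ 1 patients experience an acute LDRT associated SAE, an additional 5 patients for a total of 10 will be enrolled".
- **Section 6.1.2 (DSMC)**: the committee is to "review the outcome of each of the first 5 patients in each cohort at 24h following treatment". The next sentence stops the study if more than one of the first five has a related SAE. That sentence carries neither a time limit nor the word *acute*.
- **Section 17.9 (DSMC)**: the count is of related SAEs within 24h in the first five patients of cohort 1, and it decides whether cohort 2 may open.

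For the second five patients, section 6.1.2 says only: "Any SAE observed in any of the additional patients will be reported to the DSMC for review and discussion". Sections 7 and 17.9 add that the DSMC is told of every SAE, convenes inside 24 hours, and settles causality jointly with the investigator. Section 17.9 also gives the chair the decision to continue or halt after a monitoring review.

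Section 6.1.6 has safety monitored daily for 14 days. On the choice of numbers, section 15 says "Sample size is based on having sufficient patients to reasonably provide descriptive data for feasibility, toxicity and indication of efficacy". No unacceptable SAE rate is given anywhere.

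**The concern.** Safety is a primary objective, and this gate is the only numeric protection in the trial. If the counting window depends on the section being read, the DSMC can reach opposite enrolment decisions from the same data. If the halt scope also varies, a crossing in one cohort may or may not stop the other.

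Every number in the rule refers to the first five patients. Half of each full cohort is treated with no preset count, and the protocol gives no reason for dropping the count after patient five. Events between 24h and Day 14 are collected, but sections 15 and 17.9 do not let them bear on expansion.

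**Working it through.** **1. One set of data, five texts.** Suppose two of the first five patients have related SAEs on Day 3 and none within 24h.

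| Text | Count | Decision |
|---|---|---|
| Section 15 | 0 at 24h | Treat five more |
| Section 17.9 (if cohort 1) | 0 within 24h | Cohort 2 may open |
| Section 1.1 | 2 if Day 3 is *acute*, otherwise 0 | Halt that cohort, or expand |
| Section 6.1.1 | 2 if Day 3 is *acute*, otherwise 0 | No expansion, or expand |
| Section 6.1.2, as worded | 2 | Halt the study |

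The protocol never ties *acute* to a number of hours. Section 7 uses the word only in contrast to late toxicity.

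**2. Chance of passing the five-patient gate.** The protocol states no operating characteristic, so there is no figure to reproduce. Inputs are n = 5 and pass if at most 1 (section 15). The true rate p within the counting window is my assumption, shown as a range. Patients are taken as independent with a constant rate.

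P(pass) = (1−p)^5 + 5p(1−p)^4

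At p = 0.30 this is 0.16807 + 0.36015 = 0.528. The other values are in the table under step 4.

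**3. Effect of the window.** Suppose 30% is the rate over all follow-up and only a share of events falls within 24h (shares assumed). The rate seen by a 24h gate is then 0.30 × share:

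- share 75%: p = 0.225, P(pass) = 0.685
- share 50%: p = 0.15, P(pass) = 0.835
- share 25%: p = 0.075, P(pass) = 0.952

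The choice between 24h and a longer window is therefore not cosmetic.

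**4. Patients 6–10.** One related SAE in the first five and five in the next five (6 of 10) crosses no preset count. At p = 0.30, given a pass, the chance of at least three related SAEs among ten is 0.1973 / 0.5282 = 0.374.

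As an illustration only, let a third cumulative event halt the cohort, with the window unchanged. The chance of completing ten patients without crossing is the sum over k = 0, 1 of P(k of first 5) × P(at most 2−k of next 5):

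| True rate | Passes gate at 5 | Completes 10, third-event boundary | Difference (points) |
|---|---|---|---|
| 5% | 97.7% | 97.2% | 0.5 |
| 10% | 91.9% | 88.7% | 3.2 |
| 20% | 73.7% | 61.1% | 12.7 |
| 30% | 52.8% | 33.1% | 19.7 |
| 40% | 33.7% | 14.0% | 19.7 |

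Differences are taken before rounding.

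**5. Cost if the window is also widened.** If an assumed 5% within 24h becomes 10% by Day 14, the relevant change is 97.7% to 88.7%, or 9 points. If 10% becomes 20%, it is 91.9% to 61.1%, or about 31 points. These are upper bounds, because they assume that every event is known in time.

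**The case against.** The strongest reply is that a formal safeguard does exist after patient five. Any SAE, at any time and in any patient, brings a DSMC meeting within 24 hours with joint causality adjudication, and the chair can halt. This stands. A reader might infer from section 6.1.2 alone that nothing formal stops the trial later; sections 7 and 17.9 do not support that. What is missing is a preset count, not oversight. In a descriptive pilot with at most five more patients per cohort, leaving the decision to the DSMC is defensible if the protocol says so.

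Second, the primary safety endpoint (section 5.1.3) is set at 24h, and the halting sentence in section 6.1.2 follows directly on a 24h review, so 24h may be what was meant throughout. That is plausible, but the reader has to supply it. The halting sentence has no window and *acute* is undefined.

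Third, the benefit of a further boundary is limited. By enumeration, the illustrated rule spares on average 0.25 patients per cohort at a 30% rate, 0.14 at 20% and 0.03 at 10%. At 30%, 5.8 of the 19.7 points come from crossings on the tenth patient, when nobody is left to spare. Sections 4.1 and 4.2 also expect little acute toxicity, and at 5% the figures barely move. This stands as a reason to leave the choice of boundary to the sponsor and DSMC. It does not answer the conflict of windows.

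**Conclusion.** The halting rule contradicts itself on the counting window and on what is halted, and the same data can lead to opposite enrolment decisions. This rests on the text alone. No pre-specified count covers patients 6–10, so later stopping is discretionary.

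The pass probabilities of 92, 74, 53 and 34% at 10, 20, 30 and 40% are per cohort. They assume independence and a constant rate, and the rate is the one within whichever window is adopted. None of those rates comes from the protocol.

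Two further readings are tempting but not supported. One is that the protocol sets a 20% limit: it sets a count, and the smallest observed proportion that halts is 2/5 = 40%. A third-event boundary is therefore an illustration, not a consequence of the plan. The other is that the lack of confidence intervals in section 16, which names "frequency and percentage for categorical endpoints", is a defect. Exact intervals are optional and may sit in a SAP that is not at hand.

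**What to change.** 1. Reconcile sections 1.1, 6.1.1, 6.1.2, 15 and 17.9 to one counting window and define *acute* by it. State whether related SAEs in the first five patients that are reported after 24h count toward the halt.
2. State one halt scope, the cohort or the study. The same edit should cover section 17.9, which ties the count to cohort 1 and to opening cohort 2, whereas section 6.1.2 reviews both cohorts and section 11 enrols them simultaneously.
3. For patients 6–10, the sponsor and DSMC should either pre-specify a cumulative boundary and put its operating characteristics in section 15, or state that halting there is at DSMC discretion under sections 7 and 17.9.

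The cost is wording in five places and, if a boundary is chosen, one short table. No patients or visits are added. With a third-event boundary and an unchanged window, unnecessary pauses rise by about 3 points at a true 10% rate and about half a point at 5%. Widening the window to Day 14 would cost more. Section 2 puts mortality in ventilated patients at 50–80%, so late SAEs with disputed attribution should be expected and weighed when the window is chosen.
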